### **2.6.3 Estimands**

Defining an estimand framework was considered for this trial. Since this is an early-phase feasibility trial where the primary aim is to assess the feasibility of implementing a full PASTI trial, we will not focus on defining an estimand framework at this time. The results of this feasibility trial will help inform definitions of populations, intercurrent events, and other estimand framework attributes for a full PASTI trial.

#### **2.6.4 Primary comparisons of between-group differences**

The following primary comparisons will be reported for each secondary outcome:

1. PASTI vs Bedtime Box
2. PASTI vs No Intervention

#### **2.6.5 Distributional assumption checks**

Modelling assumptions will be checked using visual methods (i.e. plots of residuals to check if residuals are normally distributed, scatterplots of standardised residuals to check homoscedasticity).

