## **1. Description of the trial**

This is a single-centre three arm randomised controlled feasibility pilot comparing Parent-Administered Screen Time Intervention (PASTI) against a dummy Bedtime-Box arm and a No-Intervention arm in 17-31-month-old infants who have parent-reported screen time in the hour before bed. Participating families will be recruited from Central/Greater London and surrounding areas and undergo baseline assessments at home and in the lab at the Centre for Brain and Cognitive Development (CBCD) at Birkbeck, University of London. Participants will be randomly allocated (1:1:1) to one of three treatment arms: PASTI, Bedtime-Box, or No-Intervention. Follow-up home and lab assessments will be collected 6-7 weeks after baseline. The main objective of this feasibility trial is to estimate parameters required for planning a definitive trial (e.g. recruitment and randomisation rates). Secondary objectives include obtaining preliminary effect estimates of PASTI on toddler screen time, sleep, and attention control outcomes. More details are provided in the trial protocol.

This statistical analysis plan (SAP) describes the quantitative analyses that will be carried out by the trial statisticians. This does not include qualitative analysis from interviews that will be analysed separately. The statistical analysis plan was drafted and reviewed by blinded trial statisticians per the King's Clinical Trials Unit (KCTU) Standard Operating Procedures (SOP) related to statistical analysis plans [ST-02 Version 3.0]. The trial team will follow KCTU SOPs.

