## 1.8 Sample size estimation (including clinical significance)

In line with guidance on feasibility studies, no power calculation has been carried out [1]. A sample size of 60 to 100 has been shown to be sufficient in a feasibility trial [2]. A target sample size of 105 (N=35/arm) will be enrolled and randomised.

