### 1.9.2 Secondary outcomes:

We will estimate preliminary PASTI effect sizes on the following outcomes at the Weeks 6-7 follow-up home and lab visits:

1. Total infant night-time sleep duration (minutes) using actigraphy (averaged across the 7-9 day actigraphy period immediately preceding the lab visit)
2. Exogenous attention control (single search saccadic reaction time from the Visual Search Task)
3. Average toddler screen use (minutes) in the hour before bed (measured using responses from one weekday and one weekend bedtime activity diary directly preceding the lab visits and with the following formula:  $[\text{average weekday screentime} * 5] + [\text{average weekend screentime} * 2] / 7$ )
4. Additional sleep outcomes:
  - a. Average day-time nap duration (minutes) using actigraphy
  - b. Frequency of night awakenings using actigraphy (averaged across the 7-9 day actigraphy period immediately preceding the lab visit)
  - c. Sleep efficiency (total night time sleep duration expressed as a percentage of time in bed, averaged across the 7-9 day actigraphy period immediately preceding the lab visit) using actigraphy
  - d. Parent-reported sleep onset latency (minutes) from the BISQ-R
5. Additional attention control outcomes (reaction times in milliseconds):
  - a. Prosaccade saccadic reaction time from the Antisaccade Task
  - b. Proportion of antisaccades from the Antisaccade Task
  - c. Baseline saccadic reaction time from the Gap-Overlap Task
  - d. Disengagement saccadic reaction time from the Gap-Overlap Task
  - e. Parent-reported inhibitory control subscale score from the ECBQ
  - f. Parent-reported effortful control global score from the ECBQ

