### **2.6.2 Treatment Effects**

#### **2.6.2.1 Continuous outcome data**

Outcomes will be analysed with crude and an adjusted multivariable linear regression analysis. Fixed effects included will be: dummy treatment variables; baseline values of continuous outcomes; minimisation factors (child age group, child sex, family IMD quintile).

The treatment group mean difference (MD) for unstandardised effect sizes and 95% confidence intervals will be presented for both crude and adjusted estimates. Given the sample size and purpose of this feasibility trial, these estimates will not be the basis for inferential statements and p-values will not be reported. The purpose of our effect size estimates is to illustrate the size of effects across a number of possible outcomes.

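### Pre-bed screen use: the plan pools the residual variance across arms and names no action if the homoscedasticity check fails, so the 95% CIs may have the wrong width

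*SAP*

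**What the plan says.** Secondary outcome 3 in SAP section 1.9.2 is "Average toddler screen use (minutes) in the hour before bed", computed from one weekday and one weekend diary before the lab visit, weighted 5 to 2.

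Section 2.6.2.1 says "Outcomes will be analysed with crude and an adjusted multivariable linear regression analysis". Its model terms are indicator variables for arm, the baseline value and the three minimisation factors. On output it says "The treatment group mean difference (MD) for unstandardised effect sizes and 95% confidence intervals will be presented", for crude and adjusted estimates alike. It names no robust or arm-specific variance.

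Section 2.6.5 says "Modelling assumptions will be checked using visual methods" and lists scatterplots of standardised residuals as the check on homoscedasticity. It does not say what follows if the check fails. Other parts of the SAP do attach a consequence to a finding: section 2.6.2.3 moves from Poisson to negative binomial under overdispersion, and section 2.11 sets a 0.5 SD imbalance as the trigger to consider a further adjusted model.

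Section 2.6.4 makes PASTI vs Bedtime Box and PASTI vs No Intervention the primary comparisons. Section 2.11 makes Bedtime Box vs No Intervention exploratory.

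**The concern.** One linear model with arm indicators estimates a single residual variance from all three arms and uses it for every contrast. That is sound when the arms have similar spread. Here the outcome has a floor at zero, and one arm receives an intervention meant to bring it to that floor. Such an intervention changes the spread of the arm as well as its mean, so equal variances would be a coincidence.

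What is at stake is whether intervals labelled 95% for this outcome cover about 95%. Timing matters too. Section 2.13 lets the junior statistician review data by arm once the SAP is approved, so a choice of standard error left open now could be made after arm-level data have been seen.

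**Working it through.** **Inputs from the SAP.** Section 1.8: "A target sample size of 105 (N=35/arm) will be enrolled and randomised"; 3 × 35 = 105 agrees. Section 1: "Participants will be randomly allocated (1:1:1) to one of three treatment arms". The green zone for retention in section 2.4 is at least 75%, and 0.75 × 105 = 78.75, or about 26 per arm. Section 1.8 also says "no power calculation has been carried out", and no SD is given for any arm, so the plan has no figure of its own to reproduce.

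**Assumptions.** All SDs, means and baseline correlations below are assumed. The two control arms share one SD, sC; the PASTI SD is sP; r = sP/sC. In the adjusted model these stand for residual SDs.

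**Step 1: closed form, equal n per arm, no covariates.**

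- Model SE for any contrast: √[2(sP² + 2sC²)/(3n)]
- Correct SE, PASTI vs a control arm: √[(sP² + sC²)/n]
- Correct SE, Bedtime Box vs No Intervention: √[2sC²/n]
- Ratio of model to correct SE: √[2(r² + 2)/(3(r² + 1))] for a PASTI contrast and √[(r² + 2)/3] for the control contrast. The sample size cancels.

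Example with SDs of 8, 20 and 20 minutes (r = 0.4): the pooled variance is (64 + 400 + 400)/3 = 288. The ratios are √(576/464) = 1.11 and √(576/800) = 0.85.

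Approximate coverage is 2Φ(1.983 × ratio) − 1, with 1.983 the 97.5% t point on 102 degrees of freedom. This approximation returns 95.3% when r = 1.

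| r | PASTI contrast: SE ratio, coverage | Bedtime Box vs No Intervention: SE ratio, coverage |
|---|---|---|
| 0.25 | 1.14, 97.6% | 0.83, 90.0% |
| 0.40 | 1.11, 97.3% | 0.85, 90.8% |
| 0.50 | 1.10, 97.0% | 0.87, 91.4% |
| 0.60 | 1.08, 96.7% | 0.89, 92.2% |
| 0.75 | 1.05, 96.2% | 0.92, 93.3% |
| 1.00 | 1.00, 95.3% | 1.00, 95.3% |
| 1.25 | 0.96, 94.4% | 1.09, 96.9% |

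**Step 2: which r is plausible?** Let a fraction a of PASTI families be at zero and the rest have mean m and SD s. Then sP² = (1 − a)s² + a(1 − a)m². Assume a control mean of 30 and SD of 15 minutes.

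- a = 0.7, rest unchanged: 0.3 × 225 + 0.21 × 900 = 256.5, so sP = 16.0 and r = 1.07.
- a = 0.5, rest unchanged: 0.5 × 225 + 0.25 × 900 = 337.5, so sP = 18.4 and r = 1.22.
- a = 0.7, rest halve their use (mean 15, SD 7.5): 0.3 × 56.25 + 0.21 × 225 = 64.1, so sP = 8.0 and r = 0.53.
- a = 0.5, rest halve their use: 0.5 × 56.25 + 0.25 × 225 = 84.4, so sP = 9.2 and r = 0.61.

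So r can lie on either side of 1, depending on how many families reach zero and what the others do.

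**Step 3: simulation.** The first four rows use an outcome bounded at 0 and 60 minutes, control mean 25 and SD 15 before truncation, baseline correlation 0.5, arm and baseline in the model, 35 per arm and 3,000 runs. The Monte Carlo standard error is √(0.95 × 0.05/3000) = 0.4 percentage points. The last row uses SDs of 8/20/20, baseline correlation 0.4, all the plan's covariates and 2,500 runs. Coverage is listed for PASTI vs Bedtime Box / PASTI vs No Intervention / Bedtime Box vs No Intervention.

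| Scenario | Pooled variance | HC3 |
|---|---|---|
| 95% at zero, rest unchanged | 96.6 / 96.5 / 92.7% | 95.6 / 95.6 / 96.2% |
| 70% at zero, rest halved | 97.1 / 96.0 / 92.5% | 95.7 / 94.7 / 95.3% |
| 70% at zero, rest unchanged | 95.4 / 94.5 / 95.8% | 96.0 / 95.2 / 95.3% |
| 50% at zero, rest unchanged | 93.3 / 94.2 / 96.6% | 94.7 / 95.9 / 94.8% |
| SDs 8/20/20, full covariates | 96.5 / 97.2 / 91.4% | 95.9 / 96.5 / 96.3% |

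At 26 per arm the pattern is the same. With 70% at zero and the rest halved, pooled coverage is 96.3 / 96.1 / 91.4%. With 50% at zero and the rest unchanged, it is 94.0 / 93.8 / 97.1%.

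**The case against.** The strongest reply is that the error is unproven and small. The SAP gives no SDs. The analysis population in section 2.7 does not exclude non-adherent families, and the adherence target in section 2.4 is partial: green needs only 70% of PASTI families reporting no screen time on at least 60% of completed questionnaires. Homoscedasticity is named as something to check, and section 2.11 allows extra analyses to test an assumption. Section 2.6.2.1 rules out inferential statements and p-values.

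Most of this stands, and it limits the point in three ways.

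- **Direction.** A reader might infer that PASTI intervals must be too wide and the control contrast too narrow. The documents do not support that. It needs a PASTI SD below the control SD, and under partial adherence the SDs can be equal or the order can reverse.
- **Scope.** A reader might extend the point to all the linear models. The mechanism concerns screen use. Nothing in the SAP suggests unequal arm variances for the sleep or reaction-time outcomes. The antisaccade percentage may rest on as few as 5 valid trials, but unequal precision between children is not unequal variance between arms.
- **Consequence.** A reader might infer that planning of the definitive trial is distorted. Sections 1.1.1 and 2.1 base planning on within-arm means and SDs, and the outcomes named for powering are night-time sleep duration and visual-search reaction time. Pooling the residual variance changes neither those SDs nor the point estimates.

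The reply does not close the gap. The extra analyses in section 2.11 are discretionary, and a plot with no stated consequence fixes nothing. That the direction cannot be known in advance is a reason to choose an interval that does not depend on equal variances.

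**Conclusion.** The point holds for secondary outcome 3. The pooled-variance intervals have the wrong width whenever the arm SDs differ, and the SAP names no remedy.

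With a PASTI SD of 0.4 to 0.6 of the control SD, PASTI contrasts are about 5 to 12% too wide (8 to 11% in the closed form; simulations spread a little further). Bedtime Box vs No Intervention is then about 10 to 15% too narrow, with coverage near 91 to 92%. If many PASTI families reach zero and the rest do not change, the error is nil or reversed, and PASTI contrasts cover about 93 to 95%.

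All of this rests on assumed SDs, means and correlations. The effect is modest: the estimates are not used for inference, and the contrast with the largest under-coverage is exploratory.

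**What to change.** State in section 2.6.2.1 that the 95% confidence intervals for the screen-use model, crude and adjusted, use heteroscedasticity-robust standard errors (HC3; in Stata, vce(hc3)). Keep the residual plots in section 2.6.5 as description, so that the choice of standard error does not depend on them.

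The cost is one sentence and one software option. HC3 can be slightly conservative at this sample size, with coverage generally about 95 to 97% and no lower than about 94% in any scenario tried. Applying it to the other linear outcomes is optional, because no arm-level difference in variance has been shown for them.

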#### **2.7 Populations under investigation**

The primary population under investigation will be the modified intention to treat population. This will include participants who have completed at least one post baseline assessment time-point. Missing data will be explored and may be dealt with in a manner consistent with Jakobsen et al [4].

#### **2.8 Loss to follow-up and other missing data**

##### **2.8.1 Missing demographic and questionnaire data**

All efforts will be made to avoid missing data (i.e., sending reminders to complete questionnaires, incentives to return for follow-up). For each demographic and outcome measure at baseline and follow-up, the frequency and percentage of missing items will be reported for the total sample and by trial arm.

If there is missing baseline data, we will take an appropriate approach recommended by literature (e.g. mean imputation as described by White and Thompson [5]) before performing regression models as described above.

The number of completed twice-weekly activity diaries will be reported for the total sample and by trial arm. The proportion of completed diaries out of the total number of diaries sent will also be reported.

For the PASTI arm participants that have been asked to complete daily adherence questionnaires, the number of completed daily adherence questionnaires will be reported along with the proportion of completed questionnaires out of the total number of questionnaires sent.

##### **2.8.2 Missing items in scales and subscales**

Where available, we will use missing value guidance provided for scales. Where this is not available and prorating seems appropriate, we will prorate missing items only when there are no more than 30% missing items (i.e. for a ten item questionnaire, prorate only where one to three items are missing) by replacing the missing item values with the mean value of the complete items for each individual. We will not prorate missing items in calculating VABS subdomain scores because this would affect the basal/ceiling scoring rules.

### **2.8.3 Missing items in lab and actigraphy measures**

During baseline and follow-up home assessments, parents will be asked to fit actigraphy watches to their infant's ankle over a 7-9 day period. If data from actigraphy watches is missing, we may prorate if data is available from 70% of the home assessment period (i.e. if data on total infant night-time sleep duration is available from 7 out of 9 days, replace missing item values with the average value of the complete items for each individual).

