### **1.1 *Principal research objectives to be addressed***

#### **1.1.1 Primary objectives**

The primary aim of the trial is to assess the feasibility of implementing PASTI, compared with a Bedtime Box intervention and No Intervention, in 17-31-month-old infants who have parent-reported screen time in the hour before bed. To fulfil our primary aim, we will:

1. Assess the feasibility of conducting PASTI, including participation rate, participant randomisation, participant attrition, and intervention adherence.
2. Gain insight into parent experiences of PASTI and any barriers to adherence.
3. Estimate statistical parameters of the primary outcomes necessary to power a future large-scale, confirmatory trial, e.g. means and standard deviations of continuous outcome measures: total night-time sleep duration (actigraphy); exogenous attention control (singleton search saccadic reaction time from the Visual Search Task)

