#### **1.4.2 Blinding and planned unblinding**

Due to the nature of the interventions, participants will not be blind to treatment allocation. Participants will be asked not to discuss treatment groups with the blinded outcome assessor.

The junior trial statistician will be blind to the group allocation until trial analysis begins (and at the point of the Statistical Analysis Plan sign off). The chief investigators and the senior statistician will be blind until review of the draft trial report after database lock. The trial steering committee will be blinded and only receive open reports during meetings. The trial steering committee chair may request a closed unblinded report if there are safety concerns.

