## **2.9 *Pre-processing of actigraphy and eye-tracking data***

### **2.9.1 Actigraphy data**

Pre-processing of Actigraphy data will be done in the CamNtech MotionWare Software. The following data will be excluded before analysis:

- Periods of non-wear will be excluded using the MotionWare algorithm and parent-reported Actigraph removal on the Sleep Diary.
- Periods of external movement (e.g. car/buggy) will be excluded using the parent-reported Sleep Diary.

Actigraphy sleep analysis will be conducted using the CamNtech MotionWare software to deduce our primary and secondary sleep metrics. Daytime nap data will be excluded if any of the following are observed:

- A period of non-wear was reported during the nap period
- A period of external movement was reported during the nap period
- The parent reported that the child's day was not typical (e.g. child illness, child sleeping in different location, disturbance) using the parent-reported Sleep Diary.

Night time sleep data will be excluded if any of the following are observed:

- A period of non-wear was reported during the sleep period
- A period of external movement was reported during the sleep period
- The parent reported that the child's night was not typical (e.g. child illness, child sleeping in different location, disturbance) using the parent-reported Sleep Diary.
- The sleep period occurred on Daylight Saving Time (e.g. 30/10/2022)

Actigraph data for each participant will be excluded from all analysis if there are < 3 days day or night data, respectively for nap or sleep analysis.

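### Nights and days that an unblinded parent calls atypical are dropped from the actigraphy outcomes, and no committed analysis would show what that does

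*SAP*

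**What the plan says.** - **Exclusion of nights and days (SAP 2.9.1).** A night is dropped for reported non-wear, for reported external movement, for the daylight-saving clock change, or because the parent says the child's "night was not typical (e.g. child illness, child sleeping in different location, disturbance". Naps have a matching rule for days. The source is the parent's sleep diary.
- **Blinding (SAP 1.4.2).** Because of the nature of the interventions, "participants will not be blind to treatment allocation".
- **Outcome definition (SAP 1.9.2).** Night-time sleep duration, awakenings and sleep efficiency are each "averaged across the 7-9 day actigraphy period immediately preceding the lab visit".
- **Use of the results (SAP 1.1.1).** One primary objective is: "Estimate statistical parameters of the primary outcomes necessary to power a future large-scale, confirmatory trial". Actigraphy night-time sleep duration is one of the two outcomes named there.
- **Completeness.** Section 2.9.1: "Actigraph data for each participant will be excluded from all analysis if there are < 3 days day or night data". Section 2.8.3: "If data from actigraphy watches is missing, we may prorate if data is available from 70% of the home assessment period". Its worked example is that if sleep duration "is available from 7 out of 9 days, replace missing item values with the average value of the complete items for each individual". Neither section refers to the other.

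**The concern.** Non-wear, vehicle movement and the clock change are reasons why the watch signal or the clock time cannot be trusted. The atypical-night criterion is different. The recording may be perfectly good, yet the night is discarded because a parent judged it unusual, and a disturbed night is close to what the outcomes measure: shorter sleep, more awakenings, lower efficiency.

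At follow-up that judgement is made after randomisation by someone who knows the arm. Two routes to distortion follow. Parents in one arm may flag more readily than parents in another, or the intervention may change how often nights are disturbed. Either way the retained nights are no longer comparable between arms. The means and SDs carried forward to the definitive trial would then describe typical nights as judged by parents, with nothing in the report to show how far they differ from all valid nights.

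**Working it through.** **1. What would reveal a problem.** Three places in the SAP come near:
- Section 2.8.1 reports the frequency and percentage of missing items for each outcome measure by arm, but not by reason.
- Section 2.2 counts participants excluded from analysis with reasons. It does not count nights.
- Section 2.11 says only that an additional analysis may be carried out.

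None commits to keeping the atypical nights or to tabulating them by arm and reason. There is also a knock-on effect. A child with 7 recorded nights, 5 of them flagged, has 7 − 5 = 2 left and so falls under the three-night rule and out of the sleep analysis altogether.

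**2. Can sign or size be derived?** The SAP gives no flagging rate, no rate of disturbed nights and no sleep loss per disturbed night, so every input here is assumed. In an arm let a share *d* of nights be disturbed, each *L* minutes shorter, and let parents flag a share *r* of the disturbed nights and none of the others. The mean of the retained nights, relative to an undisturbed night, is

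f = −L·d·(1 − r) / (1 − d·r).

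*(a) No true effect, unequal flagging.*
- d = 0.1, L = 30, r = 0.3 against 0.6: −2.1/0.97 = −2.16 and −1.2/0.94 = −1.28, a spurious difference of 0.9 min.
- d = 0.3, L = 60, same r: −12.6/0.91 = −13.85 and −7.2/0.82 = −8.78, a difference of 5.1 min.
- r = 0.2 against 0.8 over the same range of d and L: 1.8 to 10.6 min (upper end: −14.4/0.94 = −15.32 and −3.6/0.76 = −4.74).
- Equal r: 0.

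The arm that flags more looks better, whichever arm that is.

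*(b) True benefit, equal flagging.* PASTI lowers d from 0.30 to 0.15, L = 60. With all nights kept the effect is (0.30 − 0.15) × 60 = 9.0 min. With r = 0.5 it is −4.5/0.925 + 9/0.85 = −4.86 + 10.59 = 5.7 min. With r = 1 it is 0.

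*(c) True harm, all disturbed nights flagged.* With d = 0.15 in PASTI against 0.05 in control and L = 60, a deficit of (0.15 − 0.05) × 60 = 6 min disappears.

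So the distortion can create a difference in either direction, hide a benefit or hide a harm.

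**3. The SD.** Removing short nights tends to narrow the spread between children, while averaging over fewer nights tends to widen it. The SAP has no within-child or between-child variance, so the net change cannot be signed.

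**4. The two completeness rules.** The smallest whole number of days meeting 70% is 5 of 7 (0.7 × 7 = 4.9), 6 of 8 (5.6) and 7 of 9 (6.3). The last reproduces the SAP's example: 7/9 = 77.8% passes and 6/9 = 66.7% fails. The exclusion rule asks for 3, whatever the period. Filling gaps with the child's own mean *m* gives (7m + 2m)/9 = m, so an averaged outcome is unchanged. The 70% sentence would matter only if it decided inclusion, and it does not say that it does.

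**The case against.** The exclusion is pre-specified and identical in all arms. Disturbance is listed beside illness and sleeping elsewhere, so it may mean an outside disruption rather than poor sleep; the diary wording is not in the SAP. The same rule applies at baseline, before allocation. Follow-up actigraphy falls in weeks 6 to 7, when early difficulties with a new bedtime routine may have settled. Typical-night sleep is a legitimate target. Non-wear and external movement also rest partly or wholly on the parent's diary. Section 2.6.2.1 reports no p-values and makes no inferential use of the effect estimates.

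Most of this limits the point without removing it. A common rule protects only if flagging and disturbed nights are alike across arms. It also means there is no case for insisting that all nights become the main estimate.

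Two stronger readings are tempting. A reader might infer that the exclusion favours PASTI, because removing screens could unsettle bedtimes. The SAP does not support a direction, and case (b) above goes the other way. A reader might also infer that the two completeness rules contradict each other. With independent nights each valid with an assumed probability of 0.9, 0.8 or 0.7, the share of children between the thresholds would be 2.6%, 14.3% or 32.4% over 7 days (3 or 4 valid nights) and 5.3%, 26.1% or 53.3% over 9 days (3 to 6). Those children are in dispute only if falling below 70% means missing. Section 2.8.3 permits prorating at 70%; it excludes nobody. The restrictive wording belongs to the questionnaire rule in 2.8.2.

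**Conclusion.** The point holds in a moderate form. At follow-up, good recordings can be removed on an unblinded parent's report that overlaps the outcomes, and no committed analysis would show the effect. Bias in the mean difference is possible in either direction and is not demonstrated; it needs flagging or disturbed nights to differ by arm. The minute figures above illustrate the mechanism under assumed inputs and are not estimates for this trial. The consequence is limited by the absence of hypothesis tests, but sleep duration is one of two outcomes whose parameters are meant to power the next trial.

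The completeness rules are unreconciled rather than contradictory. Read literally, every child with three or more valid nights has a sleep outcome, and the 70% sentence changes neither the analysed set nor any average. That part is a clarification only.

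**What to change.** 1. In section 2.9.1 or 2.11, commit to an analysis of each actigraphy outcome that keeps nights and days failing only the atypical criterion. Exclusions for non-wear, external movement and the clock change stay.
2. Report its means, SDs, between-arm differences and numbers of children beside the typical-only results. For awakenings, report the rate ratios planned in 2.6.2.3 as well. The typical-only analysis may remain the main one.
3. Tabulate excluded nights and days by arm, timepoint (baseline, follow-up) and reason. Score and retain the flagged nights during pre-processing so that this can be done.
4. As a clarification, state that the three-day/night rule in 2.9.1 alone decides inclusion, and delete the 70% prorating sentence in 2.8.3 for averaged outcomes.

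The cost is a few lines of SAP text, one extra run and one table, with no new data collection. The downside is that illness and away-from-home nights add noise to the added analysis, which should therefore be read alongside the typical-only one.
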